## Abstract

**Introduction:**

Approximately 1 in 13 Australian children have a neurodevelopmental disability. This project aims to assess the effectiveness and implementation of an online parenting support programme, Parenting Acceptance and Commitment Therapy (*PACT*) *Online,* for parents of children with neurodevelopmental disabilities for improving the parent–child relationship and parent and child outcomes.

**Methods and analysis:**

This hybrid type 1 randomised controlled trial will focus on evaluating intervention effectiveness and understanding the context for implementation. The primary outcome is observed emotional availability within parent–child interactions assessed at postintervention (12 weeks postbaseline) with additional measurement at follow-up (6 months postbaseline). Secondary outcomes include (1) parent-reported emotional availability, (2) parental mindfulness, (3) parent mental health, (4) psychological flexibility, (5) adjustment to child’s disability, (6) health behaviour and (7) regulatory abilities as well as child outcomes of (1) mental health, (2) adaptive behaviour and (3) regulatory abilities. Evaluation of implementation will include an economic evaluation of costs and consequences, and an implementation analysis grounded in the consolidated framework for implementation research with a focus on contextual factors influencing implementation.

**Ethics and dissemination:**

Ethical approval has been obtained from the University of Queensland Human Research Ethics Committee (023/HE000040). Dissemination of study outcomes will occur through the appropriate scientific channels. Long-term implementation will be grounded within the implementation analysis and occur in partnership with the partner organisations and consumer engagement panel. This will include releasing the *PACT Online* intervention as a massive open online course on the edX platform if support for intervention effectiveness and implementation is found.

**Trial registration number:**

ACTRN12623000612617; this trial has been registered with the Australian New Zealand Clinical Trials Registry.

STRENGTHS AND LIMITATIONS OF THIS STUDYThis study is an appropriately powered randomised controlled trial of an online intervention that has already been successfully piloted.Outcomes include a parent–child interaction observation coded by accredited coders blinded to condition, parent report measures and parent and child heart rate variability as a physiological marker of self-regulation.Adoption of a waitlist control design (for ethical reasons) means that it will not be possible to conduct further follow-up of research participants limiting potential for conclusions to be drawn beyond the 6-month follow-up period outlined in this protocol.This trial includes an implementation analysis with the aim of identifying relevant contextual factors influencing implementation and implementation strategies.

## Introduction

 Approximately 1 in 13 Australian children^1^ have a neurodevelopmental disability (NDD) including cerebral palsy (CP), autism, fetal alcohol spectrum disorder (FASD), attention-deficit hyperactivity disorder (ADHD) and intellectual disability. NDDs are lifelong and require ongoing support at significant cost (approximately $A35 000 per child per annum).^2^ Children with NDDs have a four to fivefold increased risk of poor mental health including behavioural problems^3^ and a 2-fold to 20-fold increased risk of poor physical health.^4^ In addition, they are at increased risk for adverse life outcomes in education and employment.^5^

### The family context of NDDs

There is a wealth of research demonstrating that parenting is important and that supporting parents improves child development and mental health.^6^ For children with NDDs, parents are essential partners in the delivery of health and educational supports, services and interventions.^7^ That is, effective support for children relies on parental implementation and ‘good parenting’. Parents seek supports, manage their child’s interdisciplinary health and educational teams, advocate for their child at school and in community contexts and implement programmes and strategies in the home. More recently, in Australia, parents select supports and services for their child on the National Disability Insurance Scheme (NDIS).^8^ Supports for the child may bottle-neck if there are limitations in parent capacity for implementation or challenges within the parent–child relationship.^9^

As is true of all parents, the ability of parents of children with NDDs to parent well is underpinned by their own physical and mental health.^10^ Parents of children with NDD are at a four to fivefold increased risk of compromised physical and mental health^11^ and many experience a grief that may compromise their own well-being and parenting.^12^ Ongoing psychological adaptation and complexity, including increased demands on the parent, discrimination or social isolation, can increase over time and can lead to a lifestyle that is detrimental to the health and well-being of parents,^13^ with flow-on effects for parenting and the parent–child relationship.

NDDs also impact on the emotional availability of the parent–child relationship; that is, the emotional signalling within the relationship, through the child.^14^ Children with NDDs can be slower to respond to parental cues, can cue in an atypical way or be less skilled at eliciting their parent’s involvement.^15^ Understandably, parents may respond by becoming more directive and intrusive, a phenomenon that is not in the child’s best interests as it does not encourage growth of the child’s initiative. Thus, the parent–child relationships of families of children with NDD require support, but support that is appropriate to their specific challenges.

Despite this, parenting support is not offered as standard for families of children with NDDs, and in Australia, the NDIS does not fund parenting interventions.^8^ Parents of children with NDDs are forced to seek mental health support through the general health system, a process that many report does not meet their needs.^16^ Parents of children with NDDs want specialist support for their mental health, well-being and parenting concerns: support that is focused on the specific challenges of parenting a child with an NDD and is accessible and flexible in delivery.^16^

### Tailor-made parenting support grounded in acceptance and commitment therapy

Parenting support is important for families of children with NDDs and parenting interventions are effective for families of children with NDDs.^17^,^19^ Specifically, parenting interventions incorporating Acceptance and Commitment Therapy (ACT) have been found to be effective for families of children with NDDs including acquired brain injury,^17 20^ autism^21 22^ and CP,^19 23^ both offered as standalone^21 22 24^ and in combination with behavioural parenting interventions.^19 23^ ACT is a form of cognitive behavioural therapy focused on enhancing an individual’s psychological flexibility^25^ or the ability to persist with or change behaviour, with full awareness of the present moment and in the service of chosen values.^26^ Core to ACT is acknowledgement of the universality of suffering, and the importance of living a meaningful life through effective action and focusing on what works, themes that resonate for many parents of children with NDDs.

This paper reports the protocol for a type-1 hybrid randomised controlled trial (RCT) of *Parenting Acceptance and Commitment Therapy (PACT) Online*: tailor-made ACT-based parenting support developed specifically for parents of children with NDDs that has been built for ease of implementation in existing health and disability systems. We trialled an early version of *PACT Online* with 68 families of children aged 2–12 years with CP, demonstrating an intervention effect of improved emotional availability in the parent–child relationship; specifically, reductions in parental intrusiveness and improvements in child involvement^24^ exactly the aspects of emotional availability at risk in NDD.^15^ In addition, we also found improvements in parental mindfulness and parent-reported child quality of life in the ‘well-being and acceptance’ and ‘participation and physical health’ domains.

### Aim

This hybrid type 1 RCT will test the effectiveness and implementation of *PACT Online* with families of children aged 0–10 years diagnosed with, or with an increased likelihood of, an NDD, compared with a waitlist control (care as usual; CAU) group.

### Hypotheses

We hypothesise that families allocated to the *PACT Online* group, compared with families in the CAU group, will show improved emotional availability on the observational measure of the Emotional Availability Scale (EAS;^15^ immediately postintervention (T2; 12 weeks postbaseline, primary outcome). Furthermore, we predict that this effect will be sustained at follow-up (T3; 6 months post-baseline).

We hypothesise that families in the *PACT Online* group, in comparison to CAU, will show improved parent-reported emotional availability on the Emotional Availability–Self-Report (EA-SR;^27^ as well as improved parent outcomes across measures of (1) parental mindfulness, (2) parent mental health, (3) psychological flexibility (4) adjustment to child’s disability, (5) health behaviour and (6) regulatory abilities and improved child outcomes across measures of (1) mental health, (2) adaptive behaviour and (3) regulatory abilities at T2 (12-week postbaseline) and T3 (6-month postbaseline).

To describe and understand the context for implementation, we will consider the costs and consequences as well as the contextual factors that may influence implementation. Analysis of contextual factors will be guided by the consolidated framework for implementation research (CFIR)^28^ and will consider feasibility, acceptability and appropriateness of PACT Online, sustainability potential and contextual factors that could impact on implementation success.

## Methods and analysis

### Study design

This study is a hybrid type 1 RCT. A type 1 hybrid is focused on effectiveness while also exploring implementation. We will conduct an RCT of *PACT Online* with 300 families of children with NDD. This is a two-arm RCT in which families of a child (0–10 years) with a diagnosis of an NDD or assessed as having an increased likelihood of an NDD will be randomly assigned to *PACT Online* or CAU, with follow-up until 6 months postbaseline. All families will complete assessment at preintervention baseline (T1), immediate postintervention outcome (T2; 12 weeks postbaseline for CAU group) and follow-up (T3; 6 months postbaseline). As the *PACT Online* programme is secure and unable to be accessed by external parties during the study period, no between-group contamination is possible. Consolidated Standards of Reporting Trials guidelines will inform the conduct and reporting of this RCT (see figure 1).

**Figure 1 F1:**
[figure not shown]
Consolidated Standards of Reporting Trials (CONSORT) flowchart for PACT Online study. CAU, care as usual; PACT, Parenting Acceptance and Commitment Therapy.

### Recruitment

Recruitment will be conducted with cooperation from partner organisations across multiple sectors including primary care (Paeds in a Pod), community-based allied health (BUSHKids; AEIOU Foundation for Children with Autism) and parent support organisations (NOFASD Australia, CP Alliance) as well as through broad recruitment strategies including National Registers such as the Australian CP Register, the Aus-CP-CTN Centre of Research Excellence, schools and a media campaign. While researchers are situated at key centres in Brisbane, Sydney and Melbourne, due to the fully online nature of the intervention and the assessment protocols, recruitment will be possible Australia-wide. Australia-wide recruitment, recruitment through schools and deliberate recruitment from regional and rural areas via BUSHKids will maximise representativeness of the sample. It should be noted that generalisability will be limited to English-speaking families. For each family, there must be at least one parent participant where *parent* is defined by the performance of a parental role. Hence, in this study, *parent* is inclusive of custodial grandparents or stepparents. Single parent families will be eligible, where families have more than one parent or another significant familial caregiver such as a non-custodial grandparent, a secondary participant may be nominated. For families with a primary caregiver, the participation of the primary caregiver will be strongly encouraged, and they will be treated as the primary participant for assessment purposes. Informed consent will be obtained from all participating parents prior to commencement in accordance with institutional ethics procedures (see online supplemental file for a copy of the participant consent form). Recruitment began on 26 February 2024 and it is planned to continue until approximately mid-2026.

### Inclusion criteria

To participate, families must have a child 0–10 years of age with either a diagnosis of any NDD (eg, CP, Autism, FASD, ADHD) or at identified increased likelihood of an NDD on the basis of one of the following: (1) a diagnosis of developmental delay as defined by Australian NDIS (ie, substantial reduction in functional capacity) in two or more domains (ie, gross motor, fine motor, language, or personal/social); (2) an increased likelihood of CP as established through the General Movements Assessment^29^ or Hammersmith Infant Neurological Examination;^30^ (3) an increased likelihood of autism as established through the Social Attention and Communication Surveillance Revised,^31^ including the ASDetect mobile application^32^ or (4) identified as being at risk of FASD in accordance with the Australian Guide to Diagnosis of FASD.^33^ These inclusions are consistent with the latest practice and international Clinical Practice Guidelines for the early identification of CP,^34^ autism^35^ and FASD.^33^ The age range of 0–10 years was chosen, so that PACT Online could be available as early as possible, as soon as NDD was suspected to developmental delay identified.

### Exclusion criteria

The exclusion criteria have been deliberately limited to only those necessary to ensure that the sample is appropriate to answer the research question. Parents who are unable to understand the written information sheet will necessarily be ineligible for the study, as the intervention includes materials written in English and study participation also requires the completion of sets of online questionnaires written in English. Any families ineligible for the study based on language will be referred to other services, for example, parenting programmes or allied health services, as appropriate. The *PACT Online* intervention and study assessment protocols will all be conducted online. Hence, families who do not have sufficient internet access to participate in the study, either in their own homes or elsewhere, will also necessarily be ineligible and referred to other services as appropriate. No other exclusion criteria are imposed.

### Sample size

The sample size calculation is based on the between-group difference for the primary outcome, the global relationship quality score from the EAS, which ranges from 0 (worst relationship possible) to 100 (best relationship possible). Based on a previous RCT conducted by our team in 67 families of children with an NDD (CP),^24^ we assume the SD of the Global EAS will be 14.3 units, and that identifying a difference between the active (PACT) and waitlist control group of 5.0 units is clinically important. This is equivalent to a between-group difference of 0.35 SD. To achieve 80% power, 258 families (129 in each group) are required to provide outcome data (alpha=0.05). To allow for expected 11%–15% participant attrition (as experienced in our previous trials),^24^ we will recruit a total of 300 families into this RCT. Participant retention strategies will be guided by the consumer engagement panel and will include a quarterly study update. Sample size calculations were conducted using Stata statistical software V.14 (StataCorp, College Station, Texas).

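### Recruiting 300 families covers attrition up to 14%, not the stated upper bound of 15%, where 255 remain against the 258 required (minor; wrong as written)

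*Protocol article*

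**What the plan says.** The Sample size section of the protocol article sizes the trial on a simple two-group comparison of the global EAS score: "The sample size calculation is based on the between-group difference for the primary outcome, the global relationship quality score from the EAS". Its inputs are an SD ("we assume the SD of the Global EAS will be 14.3 units"), a target difference ("identifying a difference between the active (PACT) and waitlist control group of 5.0 units is clinically important") and the resulting standardised effect ("This is equivalent to a between-group difference of 0.35 SD"). It concludes: "To achieve 80% power, 258 families (129 in each group) are required to provide outcome data (alpha=0.05".

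The next sentence turns that requirement into a recruitment target of 300, introduced by "To allow for expected 11%–15% participant attrition (as experienced in our previous trials". The Study design section repeats the target ("with 300 families of children with NDD"). The Randomisation and blinding section gives 1:1 allocation.

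**The concern.** The requirement of 258 is a count of families with outcome data, so the recruitment target has to leave 258 after losses. The article gives the range of losses it expects, 11% to 15%, and says the range comes from the team's own previous trials. A reader will take it that 258 families remain anywhere in that range. At the upper end they do not.

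What is at stake is a planning figure. While recruitment runs, the team manages retention against this margin. The true margin is 42 families lost out of 300 (14%), whereas the sentence implies 45 (15%).

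**Working it through.** **Inputs, all from the Sample size section except allocation:** SD 14.3; difference 5.0; alpha 0.05; power 80%; required total 258 (129 per group); attrition 11%–15%; recruitment 300; allocation 1:1. The section does not say whether alpha is one- or two-sided.

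**Step 1: reproduce 258.** Standardised effect = 5.0/14.3 = 0.3497, which rounds to the stated 0.35. By the two-sided normal approximation,

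n per group = 2 × (1.960 + 0.842)² × (14.3/5.0)² = 128.4, rounded up to 129, or 258 in total.

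This matches the article exactly. A one-sided test would give 102 per group, so the article evidently used a two-sided test. The t-test version gives 129.4, hence 130 per group. The check below keeps the article's own 258.

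**Step 2: attrition that 300 can absorb.** 1 − 258/300 = 1 − 0.86 = 14.0%.

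**Step 3: go through the stated range.** Families remaining = 300 × (1 − d). Recruitment needed = 258/(1 − d), rounded up.

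| Attrition d | Remaining from 300 | Recruitment needed for 258 |
|---|---|---|
| 11% | 267 | 290 |
| 12% | 264 | 294 |
| 13% | 261 | 297 |
| 14% | 258 | 300 |
| 15% | 255 | 304 |

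The target meets the requirement up to exactly 14%. At 15% it is 3 families with outcome data short, or 4 families short at recruitment (304 − 300).

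**Step 4: effect on power.** Normal approximation: power = Φ(0.3497 × √(n/2) − 1.960), with n per group. The t-test figures use the noncentral t distribution.

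| Families with outcome data | Per group | Normal approximation | t-test |
|---|---|---|---|
| 258 | 129 | 80.2% | 79.9% |
| 255 | 127.5 | 79.7% | 79.4% |

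Within either method the loss is about half a percentage point. Setting the t-test figure at 255 against a normal-approximation figure at 258 would mix a difference of method with the effect of attrition. At the other end of the range, 267 families give 81.2% by the t-test.

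**The case against.** **The wording need not be a guarantee at the upper bound.** A planner who took the midpoint, 13%, would get 258/0.87 = 297 and round up to 300. The common shortcut 258 × 1.15 also gives 297. Either could explain the choice of 300. But neither keeps 258 families after a 15% loss, and the article names 15% as part of what it expects. These routes explain the slip without making the sentence true.

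**The shortfall is trivial.** This stands. Half a percentage point of power is small next to the uncertainty in an SD taken from one earlier trial of 67 families.

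**The planned analysis probably absorbs it.** This also stands, with a caveat. The section on statistical analysis of primary and secondary outcomes specifies a mixed model on T1, T2 and T3, while the sizing ignores baseline. If adjustment for T1 acts as in an analysis of covariance, the residual variance falls by the factor 1 − r². Making 255 families worth 258 then needs r² = 1 − 255/258 = 0.012, a T1–T2 correlation of about 0.11. The article gives no such correlation, so the actual gain cannot be computed. Only this break-even value can.

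**A stronger reading to avoid.** A reader might infer that 300 fails across the whole stated range, or that the article is wrong to call the trial appropriately powered in its list of strengths and limitations. The figures support neither. The requirement is met from 11% to 14%, and power of 79.4%–79.7% at the worst stated attrition does not undermine that description.

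**Conclusion.** Wrong as written, and minor. The recruitment target of 300 allows for attrition up to 14%. It falls short of the plan's own requirement only above that, by 3 families at the 15% upper bound. Power there is 79.7% by the normal approximation or 79.4% by the t-test, so the trial is not materially underpowered.

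The count of families rests only on the article's own figures. The power figures also assume a two-sided test, which reproduces the stated 258, and an unadjusted comparison of two equal groups at T2. No conclusion about the design or the analysis changes.

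**What to change.** Restate the attrition allowance in the Sample size section, for example: *300 families allow for up to 14% attrition; at 15% (255 families) power is just under 80% (79.4%–79.7%) for an unadjusted T2 comparison.*

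The cost is one sentence and a slightly less favourable stated margin. The recruitment target in the Study design section can stay at 300, and no extra enrolment is needed. The corrected sentence also gives the team a usable retention threshold: no more than 42 of 300 families without outcome data.

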### Randomisation and blinding

Following screening to ensure eligibility, consent and the completion of baseline assessment, families will be randomised to *intervention* or CAU using central computer-generated block randomisation (Griffith University). Allocation will occur in a 1:1 ratio and blocks will be of size 12 or 16, with size randomly selected. Neither participants nor clinicians can be blind to the group allocation, and we acknowledge this may be a confound. Scoring on the observational EAS (primary outcome) will be conducted by coders who will be blind to participant group allocation.

### Intervention: *PACT Online*

*PACT Online* is an online/telehealth parent support intervention developed in partnership with parents and focused on empowering parents as well as supporting parenting, parental mental health and the parent–child relationship. It is theoretically grounded in ACT and was developed by authors [name] and [name]. PACT Online as tested in this RCT is an enhanced and adapted intervention of PACT as tested in an RCT with 68 families of children aged 2–12 years with CP.^24^

*PACT Online* is delivered over 12 weeks via the edX platform (www.edx.org/) and six telehealth sessions. It includes core ACT content and adopts a flexible, goal-directed approach focusing on each parent’s tailored behavioural goals. Parents complete six modules over 12 weeks, a module per fortnight, with an individual telehealth session for each module. In the individual telehealth sessions trained allied health clinician provide individualised feedback and additional support, helping families to apply the content to their lives. *PACT Online* thus offers a translatable and scalable universal online support at little to no cost, with additional clinician-delivered telehealth support for families who need it. For more details, see table 1.

**Table 1 T1:** PACT Online: core content and delivery

Content	Delivery
Parents will be supported to grow *parent capacity* by cultivating *flexible, sensitive and effective parenting* through developing: Effective strategies for teaching new skills and encouraging positive behaviour Effective strategies for managing misbehaviour Effective strategies for interacting with the wider community Awareness of their own and their child’s (developing) values Awareness of effective action, ie, what *works* Insightfulness, understanding the child’s perspective Experiential acceptance, the ability to live with distressing emotions, cognitions and memories as they arise, and continue to focus on effective action Acceptance of their child and their child’s emotions, cognitions, etc. Self-compassion and achievable self-care repertoires	*PACT Online* EdX course**:** 12-week EdX course, includes videos, text, multiple choice questions, real-life activities (eg, practising mindfulness during a parent–child interaction), and a discussion board facilitated by the *PACT Online* clinicians
	Clinician support**:** Clinician consultations (30–60 min) will support parents in understanding and acting on *PACT Online* content, taking a flexible goal-directed approach.Clinician consultations will focus on parental goals, parental application in real life, overcoming obstacles and integrating flexibility into parent–child interactions. Clinician consultations will be conducted fortnightly via ZOOM. They will be recorded and assessed for adherence to protocol.
Parents will choose *three goals for change***:** (i) a parent–child relationship or parenting goal, (ii) a parental self-care or health behaviour goal and (iii) a child behaviour/adjustment goal.	

PACT, Parenting Acceptance and Commitment Therapy.

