### Fidelity

The *PACT Online* edX course is static and hence remains the same for each participant who accesses it. For the telehealth consultations, all therapists will follow a consultation manual and will obtain clinical supervision from [name], [name] and [name] to ensure fidelity. [name] will also be the therapist for some families in the study. Records of intervention delivery and online course access will be kept, and telehealth sessions will be recorded.

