### Statistical analysis of primary and secondary outcomes

The primary outcome will be analysed using mixed-model repeated-measures linear regression (multilevel modelling) with time (T1, T2, T3) and group (*PACT Online*/CAU) included as the main effects, and a time-by-group interaction term. Child will be included as a random effect to account for the repeated measures from each participant. Secondary comparisons will be conducted using linear models for continuous outcomes, logistic regression models for binary outcomes and Poisson models for count outcomes. The value of the outcome variable at baseline will be included as a covariate when appropriate. When repeated measures are analysed, the non-independence of results from the same family will be accounted for using mixed-effects models. Subgroup analyses will compare outcomes by child age and child diagnosis. Analysis will follow standard principles for RCTs with two-group comparisons using the intention-to-treat principle. In the event that >10% of outcomes are missing, we will conduct a sensitivity analysis to investigate the sensitivity of results. The pattern of missingness will be examined, and if the data are ‘missing at random’, we will use multiple imputation by chained equations, whereas if the data are determined to be ‘missing not at random’, we will use pattern mixture models.

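### PACT families are nested in therapists and control families are not, but neither the primary model nor the sample size allows for differences between therapists

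*Protocol article*

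**What the plan says.** Under Intervention: PACT Online, each family works through six modules in 12 weeks with one individual telehealth session per module, and "In the individual telehealth sessions trained allied health clinician provide individualised feedback and additional support". Table 1 describes consultations of 30 to 60 minutes built around the parent's own goals. The Fidelity section refers to therapists in the plural and says that one of the supervising team "will also be the therapist for some families in the study", so the PACT arm is shared out among several clinicians. Under Control group: CAU, control families receive their usual services and are offered PACT only after the 6-month assessment.

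Under Statistical analysis of primary and secondary outcomes, the primary model has time, group and their interaction as fixed effects, and "Child will be included as a random effect to account for the repeated measures from each participant". Secondary repeated-measures models account for dependence within a family. Therapist appears in no model.

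Under Sample size, "we assume the SD of the Global EAS will be 14.3 units", a "difference between the active (PACT) and waitlist control group of 5.0 units is clinically important", and "To achieve 80% power, 258 families (129 in each group) are required to provide outcome data". The only allowance added after that is for attrition.

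**The concern.** Families treated by the same clinician share that clinician's skill and style. If clinicians differ in what they achieve, the outcomes of their families are correlated. A child random effect describes repeated measurements on one child; it cannot describe correlation between different children seen by the same therapist. The correlation arises in the PACT arm only, so the variance of the PACT mean is understated while that of the control mean is not.

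At stake are the width of the confidence interval for the primary effect, the error rate of its test when the target is the average effect over therapists, and the meaning of the stated 80% power.

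**Working it through.** **Inputs from the article (Sample size):** SD 14.3, difference 5.0, alpha 0.05 (sidedness not stated; two-sided reproduces the plan), 80% power, 129 evaluable per arm, 300 recruited, attrition 11% to 15%.

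**Inputs assumed, because the article does not give them:** number of therapists k, therapist ICC, equal caseloads, one therapist per family.

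**Step 1: reproduce the plan.** n per arm = 2 × (1.960 + 0.842)² × 14.3² / 5.0² = 128.4, rounded up to 129, so 258 in total. The planned standard error is 14.3 × √(2/129) = 1.781, the ratio 5.0/1.781 is 2.808, and power is Φ(2.808 − 1.960) = 0.802. The stated figure is matched with independent families, so it contains no design effect. The step to 300 leaves no spare allowance either: 258/0.86 = 300, which is 14% attrition, inside the stated range.

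**Step 2: add clustering in the PACT arm.** With m = 129/k families per therapist:

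- design effect in the PACT arm: DE = 1 + (m − 1) × ICC
- variance ratio for the difference: R = (DE + 1)/2
- actual two-sided level of the nominal 5% test: 2 × [1 − Φ(1.960/√R)]
- power with the correct standard error: Φ(2.808/√R − 1.960)

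Example, k = 6 and ICC = 0.05: m = 21.5, DE = 1 + 20.5 × 0.05 = 2.025, R = 1.51, √R = 1.230. The level is 0.111 and power is 0.627.

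| Therapists | ICC | m | R | SE ratio √R | Actual level | Power |
|---|---|---|---|---|---|---|
| any | 0 | – | 1.00 | 1.000 | 0.050 | 0.802 |
| 20 | 0.01 | 6.5 | 1.03 | 1.014 | 0.053 | 0.791 |
| 10 | 0.02 | 12.9 | 1.12 | 1.058 | 0.064 | 0.756 |
| 10 | 0.05 | 12.9 | 1.30 | 1.139 | 0.085 | 0.693 |
| 6 | 0.02 | 21.5 | 1.21 | 1.098 | 0.074 | 0.725 |
| 6 | 0.05 | 21.5 | 1.51 | 1.230 | 0.111 | 0.627 |

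(Starting from exactly 80% instead of 0.802 lowers the power figures very slightly, for example 0.754 instead of 0.756.)

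**Step 3: limits of the approximation.** The table uses one time point and a normal approximation. Small-sample degrees of freedom lower power further: for 10 therapists and ICC 0.05, from 0.693 to about 0.656. Unequal caseloads would raise the design effect. The baseline measurement in the repeated-measures model may recover some power, but it does not bring therapist variation into the standard error.

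**The case against.** Four arguments deserve weight.

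*The size is not in the document.* Therapist numbers, caseloads and ICC are all assumed, and several features should hold the ICC down: the edX course is identical for every family, therapists follow a manual under common supervision, sessions are recorded and checked for adherence, and the primary outcome is coded by blinded raters. This stands as far as size is concerned, and the benign end of the range is a real possibility. But these are delivery and measurement safeguards. They may reduce therapist variation; they do not put what remains into the standard error.

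*The test is not invalid in every sense.* A reader might infer that the trial's type I error is simply above 5%. That is too strong. If PACT does nothing for any family, therapists cannot differ in its effect, and the planned test keeps its level. The inflation applies when the average effect over therapists is zero but individual therapists' effects vary around it. An analysis confined to the therapists in the trial is a legitimate, narrower target, though the article does not say that it is the intended one.

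*Wider harms are not documented.* A reader might infer that the result will be presented as holding for clinicians in partner services. No section says so; the article plans release as an open online course and an offer of training to partners. A reader might also see the clinician-facilitated discussion board as another source of clustering. The article does not say that all families share one board, and if they did, it would be a single cluster that a therapist effect could not address. The point does not rest on either argument.

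*The detail may sit in the SAP.* An article may leave further terms and sensitivity analyses to a fuller document, and the wording does not exclude them. However, the article is not silent on correlation: it names the random effect and its purpose, and deals with family-level dependence. An SAP that followed that text would carry the omission forward.

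**Conclusion.** The concern holds in a limited form. The design is partially nested, the stated primary model has no therapist term, and the stated sample size assumes independent families. If therapists differ in effectiveness, the model's standard error is too small for inference about the average effect over therapists.

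Under the assumed 6 to 10 therapists and ICC 0.02 to 0.05, the standard error is understated by a factor of 1.06 to 1.23. The article does not establish that the trial is underpowered or that the problem is large: that depends on two quantities it does not report, and with many therapists and a small ICC the effect is trivial. It is worth acting on because the remedy is cheap and returns essentially the planned model when therapist variance is zero.

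**What to change.** 1. Record a therapist identifier for each PACT family, taken from the delivery records that the Fidelity section says are kept.
2. Before analysis, prespecify a partially nested mixed model for the 12-week contrast: a therapist random effect in the PACT arm only, each control family as its own cluster, the child effect retained for repeated measures, and small-sample degrees of freedom.
3. If therapists are too few for the variance to be estimated stably, keep the planned model as primary and run the partially nested model as a prespecified sensitivity analysis.
4. Report the number of therapists, their caseloads and the therapist ICC.
5. State beside the sample size that the 80% power assumes no therapist clustering.

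The cost is one data field and some analysis wording. The downside is possibly wider intervals and a less favourable statement of power. No change to recruitment is asked for.
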